### **Primary outcomes**

The primary outcomes are:

· Changes from baseline to the 9-month follow-up assessment in positive and negative symptom severity and subjective appraisal, as measured by the positive and negative subscales of the PANSS and by the PSYRATS.

· Relapse occurrences during the period between baseline and the 9-month follow-up assessment, where relapse is defined as an episode that has resulted in an admission to a psychiatric inpatient unit (number and days of hospitalization) and/or any case noted record of re-emergence after a period of full/partial remission of positive psychotic symptoms of at least moderate degree requiring a significant change in the clinical management (for example, increased visiting or medication levels) [49]. Consensus ratings will be made by paired members of the research team (blind to the randomization arm) using *a priori* operational definitions.

In this pragmatic trial, two primary outcome measures were defined in order to detect more finely-tuned clinical changes also in those patients (nearly 60%) [50] who are not expected to relapse over the study period, and in those who have a continuous course of illness.

In addition to relapse occurrences, the number of months in full or partial remission will be calculated in a randomly selected subsample of 30% of the participating subjects. This will be obtained by means of a published method for rating remission in psychosis that has been used in previous randomized controlled trials [18,49,50]. Consensus ratings will be made by paired members of the research team using manualized *a priori* operational definitions, a method with good validity and moderate to good reliability [18,49]. Ratings are based on the level of positive psychotic symptoms, and the technique will be applied to detailed extracts of the clinical case notes. These will consist of monthly reports over 9 months on mental state and service interventions, from which all information identifying the location of the clinical service and the nature of treatment will have been removed. Actual group allocation will remain concealed until all ratings are complete. Data on all hospital admissions will be retrieved from the hospital discharge records administrative database.

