### **Interventions**

#### ***Experimental treatment***

The experimental treatment package is provided by routine public CMHCs, which operate within the Italian National Health Service and consists of TAU (see next paragraph) plus evidence-based additional treatment. Specifically, the additional treatment comprises three main forms of intervention: 1) cognitive behavioral therapy for psychosis (CBTp) for patients; 2) family intervention for psychosis (FIp); and 3) case management (CM).

CBTp is based on the model developed by Kuipers *et al.*[17], Garety *et al.*[18] and Fowler *et al.*[19], and the model has already been evaluated in randomized controlled trials [20]. It is expected that an optimal number of 20–30 CBT sessions per patient will be delivered during a time frame of 9 months, with weekly sessions held during the first 3 months and fortnightly during the following 6 months. Family intervention is based on the model proposed by Leff *et al.*[21] and further developed by Kuipers *et al.*[22]. It consists of an optimal number of 10–15 sessions over 9 months with each individual family: 6 sessions in the first 3 months, and at least 1 session/month during the following 6 months. For case management, every patient/family has a dedicated case manager, who coordinates all planned interventions.

Experimental interventions are expected to begin as soon as the patient is stabilized (clinical stabilization is defined as a condition allowing the patient to collaborate in at least a brief clinical examination) and after he/she has been assessed with the ‘core’ set of baseline measures (see ‘Baseline assessment’ below). Before the start of the trial, professionals using the experimental interventions received specific training programs in CBTp (conducted as part of the scientific aims of the GET UP PIANO Project), FIp, and CM (conducted as part of the scientific aims of the GET UP TRUMPET Project). At the end of the training, an assessment of the competence achieved was performed, and detailed intervention manuals based on international standards were developed and given to the professionals as a standard to be followed for the treatment. Professionals are supported in their clinical work by a team of expert psychotherapists assigned to each CMHC. Moreover, experimental interventions provided to all patients/relatives are supervised by a team of external experts who hold one-day meetings every 2 months and are regularly available for consultation.

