#### ***Treatment as usual***

TAU is also provided by routine public CMHCs operating within the Italian National Health Service, as above. Standard care for patients with FEP typically consists of personalized outpatient psychopharmacological treatment, combined with non-specific supportive clinical management at the CMHC level. Family interventions generally consist of non-specific informal support/educational sessions. Specialized individual psychotherapeutic interventions (including CBT) for patients and specialized psychoeducational or cognitive-oriented family interventions are usually not provided because of the lack of trained professionals [26,27].

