### **Follow-up assessment**

After a 9-month period from baseline assessment, patients are reassessed to measure: substance abuse (CDUS) [29], symptoms (PANSS [30], HAMD [31], BRMRS [32]), global functioning (GAF) [33], subjective appraisal of positive symptoms (PSYRATS) [34], social disability (DAS) [35], insight (SAI-E) [36], need for care (CAN-EU) [37] and quality of life (WHOQOL-Bref) [38] (Table 1). Patients are also evaluated in terms of pharmacological side-effects and other adverse events, pattern of clinical course (Life Chart Schedule; LCS) [46] and service satisfaction (Verona Service Satisfaction Scale, patient version; VSSS-EU) [47].

Family members are reassessed with respect to burden of care (IEQ-EU) [43] and emotional distress (GHQ) [44], and are also assessed for service satisfaction (VSSS, relatives version; VSSS-Relatives) [47].

The formal best-estimate research diagnosis is assessed at the 9-month follow-up using the item group checklist of the SCAN [16]. All relevant baseline and follow-up information is obtained and reviewed by two independent raters to formulate the ICD-10 diagnosis. In cases where a consensus is not reached, the opinion of a third rater is solicited to clarify diagnostic problems.

Psychosocial and pharmacological treatment, together with number and days of admission provided in the 9-month follow-up period, are recorded in a detailed *ad hoc* schedule.

All patients who have terminated contact with the service before the 9-month follow-up are traced and asked to undergo a semi-structured interview on the characteristics of treatment termination (Verona Interview for Treatment Termination, VITreT). This consists of 10 questions assessing: if the decision to interrupt service contacts was shared or not with the key clinician; the reason for interruption; which type of assistance was eventually received thereafter in other settings, including admission to hospital; and satisfaction with the care provided in these settings [48].

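### Detection of case-note relapse is likely to differ by arm because the intervention itself adds service contact, and blinded rating cannot correct this

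*Protocol article*

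**What the plan says.** The Primary outcomes section gives relapse two limbs joined by and/or.

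- **Admission limb:** "relapse is defined as an episode that has resulted in an admission to a psychiatric inpatient unit". Its source does not depend on contact with the community mental health centre (CMHC): "Data on all hospital admissions will be retrieved from the hospital discharge records administrative database".
- **Case-note limb:** "any case noted record of re-emergence after a period of full/partial remission of positive psychotic symptoms of at least moderate degree", with the further condition "requiring a significant change in the clinical management (for example, increased visiting or medication levels").

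The safeguard is blinded rating: "Consensus ratings will be made by paired members of the research team (blind to the randomization arm"). The Blinding section adds that lack of blinding should have limited effect because the primary outcomes are objective.

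Contact differs by arm. Under Experimental treatment, CBT is planned at 20–30 sessions per patient over 9 months, "with weekly sessions held during the first 3 months and fortnightly during the following 6 months", with 10–15 sessions for each family and a dedicated case manager. Treatment as usual is "personalized outpatient psychopharmacological treatment, combined with non-specific supportive clinical management at the CMHC level", with informal family support and no stated frequency.

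On patients who leave, Follow-up assessment says: "All patients who have terminated contact with the service before the 9-month follow-up are traced". The interview covers whether the decision was shared, the reason, later care including admission, and satisfaction. As described, it does not ask about return of symptoms. Service disengagement is a secondary outcome.

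**The concern.** A case-note relapse has to pass three steps before a rater can see it: staff learn of the symptoms, they record them, and they change management. The intervention acts on the first step by adding contact, and it may act on the third, because more visiting is one of the two examples of a qualifying change. The same services deliver the treatment and keep the notes, and their clinicians cannot be blinded.

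Blinded rating removes bias in how a given note is read. It does nothing about a difference in what the notes contain. The objectivity argument in the Blinding section fails for the same reason: this limb rests on routine notes and on clinicians' management decisions.

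At stake is the reading of a primary outcome, and of the one on which the patient sample size rests. With fuller detection in the experimental arm, a real benefit would look smaller, and equal true rates could look like harm.

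**Working it through.** **1. The plan's own figures.** Sample size and power calculations uses 25% (TAU) v 10% (experimental), two-sided 5%, 80% power, intra-cluster correlation 0.05, four patients per cluster, 10% loss and about 400 patients.

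- The stated total of about 250 under individual randomization is not reproduced. The two-proportion formula gives 200 without and 226 with continuity correction; 250 gives 88% power.
- Design effect: 1 + (4 − 1) × 0.05 = 1.15, and 250 × 1.15 = 287.5, not 350.
- 350 / 0.9 = 389, in line with about 400.

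These mismatches overstate the number needed and do not affect the present point.

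**2. Planned added contact.** Patient sessions are 20–30. The weekly-then-fortnightly schedule gives about 13 + 13 = 26. Family sessions are 10–15, and their schedule gives at least 6 + 6 = 12. The total is 30–45, but only 20–30 are with the patient, and all are described as optimal numbers. The documents give no TAU frequency, so the size of the contrast is unknown.

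**3. Observed rate under incomplete detection.** Let h be the share of relapses that are admissions (assumed fully captured in both arms) and s the case-note capture in an arm:

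observed rate = true rate × [h + (1 − h) × s]

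The documents give neither h nor s, so both are assumed. True rates are taken as 25% and 10%.

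**4. Power.** Effective n per arm = 400 × 0.9 / 1.15 / 2 = 156.5.

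Power = Φ{[|p₁ − p₂| − 1.96 √(2p̄(1 − p̄)/n)] / √([p₁(1 − p₁) + p₂(1 − p₂)]/n)}, with p̄ the mean of the two rates.

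Full detection: (0.15 − 1.96 × 0.04295) / 0.04211 = 1.56, so power is 0.94.

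| Capture TAU / experimental | h = 0: observed | Power | h = 0.5: observed | Power |
|---|---|---|---|---|
| 100% / 100% | 25% v 10% | 0.941 | 25% v 10% | 0.941 |
| 90% / 100% | 22.5% v 10% | 0.854 | 23.75% v 10% | 0.905 |
| 80% / 100% | 20% v 10% | 0.699 | 22.5% v 10% | 0.854 |
| 70% / 95% | 17.5% v 9.5% | 0.545 | 21.25% v 9.75% | 0.806 |
| 60% / 100% | 15% v 10% | 0.266 | 20% v 10% | 0.699 |

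For example, at 70% / 95% with h = 0.5: 0.25 × (0.5 + 0.5 × 0.70) = 0.2125 and 0.10 × (0.5 + 0.5 × 0.95) = 0.0975.

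**5. Equal true rates.** With 25% in both arms, 70% / 95% capture and h = 0, the observed rates are 0.25 × 0.70 = 17.5% (TAU) v 0.25 × 0.95 = 23.75% (experimental), an apparent harm of 6.25 points.

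**6. If capture ran the other way.** At 95% (TAU) / 70% (experimental) and h = 0, the planned rates become 0.25 × 0.95 = 23.75% v 0.10 × 0.70 = 7%. The 16.75-point difference exceeds the true 15, so the sign of the bias depends on which arm is better captured.

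**7. Disengagement.** Suppose 30% (TAU) and 10% (experimental) left and all their case-note relapses were missed. The observed rates are 0.25 × 0.70 = 17.5% v 0.10 × 0.90 = 9% at h = 0 (power 0.60), and 21.25% v 9.5% at h = 0.5 (0.825). These disengagement rates are also assumed.

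**The case against.** Several counter-arguments carry weight.

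- **Only part of the endpoint is exposed.** Admissions are captured whatever the contact. At 70% / 95% capture, if half of relapses are admissions, power stays near the planned 80%. This stands, and it is why the loss cannot be given as one number.
- **Direction.** Symptoms of at least moderate degree that force a change in management may reach staff in either arm, and where weekly visits are already scheduled, an increase in visiting may be harder to identify. A reader might infer that the bias must hide a true benefit; the documents make that likely, not certain.
- **Contact contrast.** A reader might take 30–45 sessions as extra patient contacts. A third of each end of that range is with the family, and TAU includes clinical management and informal family support. The contrast remains, but its size is not known.
- **Disengaged patients.** A reader might infer that they are counted as relapse-free. The article does not say so. It refers to a priori operational definitions that it does not reproduce, traces those who leave, and assumes data missing at random. A fuller rule may exist elsewhere, so its absence here is not the fault raised. The caution is that a patient with no notes has no recorded event and may not be flagged as missing.
- **Other evidence.** The other primary outcome (PANSS and PSYRATS change) is rated by independent evaluators on one schedule in both arms, and the Life Chart Schedule is collected at 9 months. It would therefore be too strong to call a null relapse result uninterpretable.
- **The planning rates** are for relapses and/or severe psychotic symptoms, and may already be observed rates. The calculation is an illustration, not a forecast.

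None of this answers the central point: blinded rating and the appeal to objectivity do not make detection of case-note relapse equal between arms.

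**Conclusion.** The concern holds in limited form. One limb of the relapse outcome depends on service contact, contact differs by arm by design, and the stated safeguards act only after the record is made. Detection is likely to be unequal, probably fuller in the experimental arm.

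Its size is not known. With 100% capture in the experimental arm and 60–90% under TAU, the observed difference falls from 15 points to 5.0–12.5 if no relapse is an admission, and to 10.0–13.75 if half are. At 70% / 95% capture, power is about 55% and 81% respectively, against 94% with full detection. All of this rests on assumed capture and admission shares, on complete admission data, and on the planned rates being true rates. It warrants an inexpensive improvement; it does not invalidate the endpoint.

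**What to change.** 1. Analyse admission relapse and case-note relapse separately as well as combined.
2. Name admission-only relapse from the hospital discharge database, counted over the same 9 months for all patients whether or not still in contact, as the key supporting analysis for the relapse outcome. It need not act as a veto: requiring agreement in direction would give a sparser endpoint too much weight.
3. In the Blinding section, qualify the statement of limited bias so that it does not extend to the case-note limb.
4. Treat patients with no notes after disengagement as having unobserved case-note status from that time, not as relapse-free. Report the event rate per month in contact as a sensitivity analysis only, since ending follow-up at last contact may be informative and does not correct for unequal contact among patients who stay.

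The cost is wording and a few extra analyses on data the plan already collects. The downside is that admission-only relapse has fewer events and is less precise.

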### **Secondary outcome measures**

The secondary outcomes will be:

· change from baseline to 9 month follow-up in patient functioning, assessed using the GAF and the WHO-DAS;

· change from baseline to 9 month follow-up patient emotional wellbeing, measured by using the anxiety and depression items of the PANSS and the HAM-D and selected items of the WHOQOL-Bref;

· service disengagement and time to service disengagement, assessed by consulting case records and local databases;

· change from baseline to 9 month follow-up in patient needs for care, assessed using the CAN

· change from baseline to 9 month follow-up in expressed emotions of the key relative, measured using the LEE

· change from baseline to 9 month follow-up in burden of the key relative, measured using the IEQ

· service satisfaction in patients and relatives, measured using the VSSS-EU and VSSS-Relatives scales.

### **Reporting and quantification of side-effects**

No specific side-effects are expected from the interventions being tested. Monitoring and registration of death (from any cause), suicide attempts, serious medication side-effects (neuroleptic malignant syndrome, tardive dyskinesia, akathisia, and tremors) for participants in both treatment arms will be maintained over the study duration. Across both arms, these adverse events will be recorded by the treating psychiatrists as they occur and by the assessors who collect data at 9 months.

### **Sample size and power calculations**

For power calculations, we consider rates of relapses and/or severe psychotic symptoms to be the primary outcome measures. For a conventional trial with randomization of individual patients [51], a total of approximately 250 patients will detect a difference in terms of rates at 9 months from 25% in the TAU arm to 10% in the experimental treatment arm, with a power of 80% (two-sided test at 5%, http://statpages.org/proppowr.html). This difference could represent a plausible and realistic intervention effect [7,52,53]. The cluster randomization used for the GET UP PIANO trial purposes might result in reduced efficiency and loss of power because the within-cluster responses tend to be more similar than those of individuals from different clusters (commonalities in selection, exposure, shared environment, mutual interaction). A larger sample size will therefore be needed to compensate for this clustering effect. The clustering effect is measured as 1 + (*m*−1)*ρ*, where *m* is the number of participants per cluster (assuming equal sizes for clusters) and *ρ* the intra-cluster correlation coefficient (ICC). This clustering effect is used as an inflation factor to increase the sample size calculated, as required by an individual randomization trial [51,54]. Our approach is simplified because it does not take into account variations in the number of participants in each cluster and assumes *m* to be the average number of participants per cluster. Although this type of imbalance in cluster size may reduce the power of the trial, the loss is negligible for studies with more than 100 patients per arm [55]. Based on the additional assumptions of an ICC of 0.05 and an average of four eligible and consenting patients in each cluster, the number of patients required would be approximately 350. With a loss to follow-up of approximately 10%, we expect that a sample size of about 400 patients will yield sufficient power. Assuming an expected incidence rate in Italy for non-affective psychoses of 11 per 100,000 per year [56] and a rate for affective psychoses rate of 6 per 100,000 per year [57], a reasonable estimate of the number of patients expected over 1 year from the 116 participating CMCHs (total population 9,203,093; at-risk population about 50%) is about 800. Assuming an attrition rate of approximately 50%, due to a number of reasons, both at the cluster level (drop-out of CMHCs from the study, lack of cooperation) and at the individual level (participants who do not seek help, do not attend the public services, refuse to be involved in the study), the number of patients available for the trial would be about 400.

With regard to family members, the key-relative burden assessed by using the IEQ was used as the outcome measure for power calculation. From previous studies [58,59], we expect the mean reduction of total IEQ score to be 8.0 in a total score range of 27 to 135 for the family members allocated to TAU, with a standard deviation of 15.0. We want to be able to detect at least a 50% greater reduction in the burden in the experimental intervention group at the 0.05 level of significance and with a power of 80%. For a conventional trial with randomization of individual subjects, a sample size of 280 will allow detection of this difference in key-relative burden. By applying the inflation factor to account for the cluster design, the sample size required would increase up to 320. Based on the expected number of patients (n = 400), it seems reasonable to assume that a 20% of family members will not be traceable, will refuse to participate, or will drop out from the trial. Thus, the expected number of about 300 family members would be sufficient to detect a significant difference in burden.

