### **Randomization procedure**

In total, 96 units entered the randomization procedure, with equal numbers being allocated to each arm. These units were randomly assigned to one of the two trial arms with a 1:1 allocation rate. The trial statistician (blind to CMHC identity) prepared the sequence of treatments (experimental treatment versus TAU) randomly permuted into blocks of two. The randomization schedule was generated using Stata software (version 11.0; Stata Corp, Corp., College Station, TX, USA), using the ‘ralloc’ command for random allocation of treatments balanced in blocks. Subsequently, arm allocation was disclosed to each CMCH, and the allocation sequence was not altered. One CMHC refused to begin the study immediately after the randomization procedure (Figure 1).

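### The requirement of about 350 patients does not follow from the plan's own inputs, which give 288; the discrepancy is conservative and the target of 400 can stand

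*Protocol article*

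**What the plan says.** All of the following is in the protocol article, section Sample size and power calculations, unless another section is named.

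- **Base.** For individual randomisation, "a total of approximately 250 patients will detect a difference in terms of rates at 9 months" of 25% under TAU against 10% under the experimental treatment, with 80% power and a two-sided 5% test. Allocation is 1:1 (Randomization procedure).
- **Inflation.** The factor is 1 + (m−1)ρ, with m the average number of participants per cluster. The text says that varying cluster sizes are left out of it, and adds that "the loss is negligible for studies with more than 100 patients per arm".
- **Result.** With ICC 0.05 and "an average of four eligible and consenting patients in each cluster, the number of patients required would be approximately 350".
- **Loss to follow-up.** About 10% is then allowed for, which leads to about 400.
- **Family members.** The individually randomised figure is 280. "By applying the inflation factor to account for the cluster design, the sample size required would increase up to 320".

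**The concern.** Every term needed to reach the clustered requirement is printed, and the terms do not produce the printed result. The two obvious explanations are closed by the text itself: cluster-size variation is expressly left out, and the 10% loss comes after the 350. The section also implies two inflation factors for one design, 1.40 for patients and about 1.14 for relatives.

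The figure will be used as a yardstick. The same section expects centre drop-out, refusals and overall attrition of about 50%, so a shortfall against 350 is a realistic event. A trial that analysed 290 to 340 patients could be judged short of its requirement although the plan's own formula and base ask for 288. A null result could also be read as coming from a trial with 80% power for 25% v 10%, when power on the stated inputs is higher.

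**Working it through.** **Inputs (protocol article):** rates 0.25 and 0.10; two-sided 5%; power 80%; 1:1 allocation; base 250; ICC 0.05; m = 4; loss 10%; printed results 350 and 400.

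**1. The plan's own step.**
- Factor: 1 + (4 − 1) × 0.05 = 1.15.
- 250 × 1.15 = 287.5, so 288 analysed.
- 288 / 0.9 = 320 recruited.
- Printed: 350 (350 / 288 = 1.22) and 400 (400 / 320 = 1.25). Only the last printed step fits: 350 / 0.9 = 389, loosely 400.

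**2. What 350 would need.**
- 350 / 250 = 1.40.
- At ICC 0.05: m = 1 + 0.40 / 0.05 = 9.
- At m = 4: ICC = 0.40 / 3 = 0.133.
- Neither is printed. With 96 randomised units, 400 / 96 = 4.2 patients per unit, which fits m = 4 and not m = 9.

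**3. The factor in the family-member calculation.** 280 × 1.15 = 322, printed as 320 (320 / 280 = 1.14). This agrees with the stated factor apart from rounding.

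**4. The base of 250.** Pooled-variance formula, n per arm = [1.96 √(2 p̄(1−p̄)) + 0.842 √(p₁(1−p₁) + p₂(1−p₂))]² / (p₁−p₂)², with p̄ = 0.175:
- n = (1.053 + 0.443)² / 0.15² = 99.5 per arm, so 200 in total.
- With continuity correction, n/4 × [1 + √(1 + 4/(n × 0.15))]² = 112.5 per arm, so 226 in total.
- Other methods at 80% power: unpooled variance 194, arcsine 193, Fisher exact about 220. None gives 250.
- Power at 250: 88.2% uncorrected, 84.5% with continuity correction, 85.5% Fisher exact.
- A 90% power base does not recover 350 either: 266 × 1.15 = 306, or 292 × 1.15 = 336 with continuity correction.

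**5. Power at the numbers expected, factor 1.15.** The 400 is derived from 116 centres and 9,203,093 inhabitants. Five centres (503,000 inhabitants) were placed in the intervention arm without randomisation, and the 400 appears to include them. Assuming equal yield per inhabitant, randomised patients number 400 × (9,203,093 − 503,000) / 9,203,093 = 378, and 378 × 0.9 = 340 are analysed.

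| Analysed | Effective N (÷ 1.15) | Power, uncorrected | Power, continuity-corrected |
|---|---|---|---|
| 288 | 250 | 88.2% | 84.6% |
| 340 | 296 | 92.8% | 90.4% |
| 350 | 304 | 93.5% | 91.3% |
| 360 | 313 | 94.1% | 92.1% |

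**6. Unequal cluster sizes.** Factor 1 + ((1 + CV²)m − 1)ρ, where CV is the coefficient of variation of cluster size. The document gives no CV, so these values are assumptions.

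| CV | Factor | Requirement from 250 |
|---|---|---|
| 0.5 | 1.20 | 300 |
| 0.7 | 1.25 | 312 |
| 1.0 | 1.35 | 338 |
| 1.2 | 1.44 | 360 |

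**The case against.** **The errors are harmless.** Both run in the safe direction, the target of 400 is unchanged, and the text says only that 400 gives sufficient power, which is true. This stands, and it limits the point to a correction of the justification. A reader might infer from an irreproducible calculation that the trial is underpowered or that 400 is wrong. The inputs show the opposite.

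**250 may be a rounded-up sufficient number.** The word approximately, and a generous rounding from 226, would make the 80% claim true though loose. That is a fair reading, so the base is weaker evidence of a slip than the step from 250 to 350. The same reading cannot rescue 350, because a gap of 22% is not rounding.

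**350 may contain a margin for unequal clusters.** A CV of about 1.0 to 1.2 would give 338 to 360. But the text says that no such allowance was made.

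**The sentence on 100 patients per arm.** A reader might infer that it is simply wrong, because the relative inflation depends on CV, m and ICC and not on patients per arm. The sentence, however, is about power, and loss of power does shrink as numbers grow. Moving from factor 1.15 to 1.35 costs about 7 percentage points at 200 patients in total, 4 at 360 and under 1 at 600 (uncorrected formula). A fixed threshold is crude, but the documents do not support calling the sentence an error.

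**The family-member calculation.** A reader might infer that its factor also needs changing. It does not: 280 to 320 is a consistent use of 1.15. It serves here only to show which factor the authors had in mind.

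**Conclusion.** The point holds as an error in the stated justification. On the printed base, formula, ICC and cluster size the requirement is 288 analysed and 320 recruited, so 350 and 400 are about 22% and 25% higher than the inputs give. The base is itself above the 80% requirement of about 200, or 226 with continuity correction. No standard variant that was tried reproduces either 250 or 350.

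Both discrepancies are conservative. The target of 400 stands, and on these inputs power for 25% v 10% is above 80%: about 90–93% at 340 analysed and 92–94% at 360. The figure of 360 should not be taken for granted as all randomised, given the five centres placed in the intervention arm; 340 rests on the pro rata assumption. These powers also assume ICC 0.05, equal clusters of four, and the binary relapse outcome only. They say nothing about the PANSS and PSYRATS outcomes, which are primary as well.

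**What to change.** 1. Replace the 350 by 250 × 1.15 = 288 analysed, 320 recruited with 10% loss. If 350 came from a different ICC, cluster size or a deliberate margin, print that input instead.
2. Keep the recruitment target of 400, and say that it exceeds the calculated requirement.
3. Either restate the base as about 200 (226 with continuity correction) for 80% power, or keep 250 and give its power of about 85–88%.
4. State the power for this binary outcome at the number expected to be both randomised and analysed, and say how the five non-randomised centres are counted.
5. If a margin for unequal cluster sizes is intended, state the assumed CV and put it in the factor; CV 0.5 to 1.0 would give 300 to 338 from a base of 250.

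The sentence on 100 patients per arm and the inflation factor for family members need no change on account of this point.

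The cost is wording only: no added patients, no new data and no change to the analysis. The authors would have to acknowledge that the printed requirement was not obtained from the printed formula.

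### The patient sample size of about 350 does not follow from its own stated inputs: 250 inflated by the stated design effect is about 288, and the discrepancy is conservative

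*Protocol article*

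**What the plan says.** All the planning inputs are in the protocol article, under Sample size and power calculations.

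- **Outcome:** "we consider rates of relapses and/or severe psychotic symptoms to be the primary outcome measures".
- **Base size:** about 250 patients in all under individual randomisation, for a fall in the 9-month rate "from 25% in the TAU arm to 10% in the experimental treatment arm"; power is set at 80% and the test is two-sided at the 5% level.
- **Clustering:** the base is multiplied by 1 + (m − 1)ρ. The section says that variation in cluster size is left out.
- **Values used:** "Based on the additional assumptions of an ICC of 0.05 and an average of four eligible and consenting patients in each cluster", which sets ρ = 0.05 and m = 4.
- **Result:** "the number of patients required would be approximately 350". A 10% loss to follow-up is then added to reach about 400, which is described only as giving sufficient power.
- **Relatives:** the inflation factor for the cluster design takes 280 to 320.

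The Primary outcomes section explains the choice of two primary outcomes by referring to patients, "nearly 60%) [50] who are not expected to relapse over the study period".

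**The concern.** The article gives the formula, both values that enter it, the starting number and the result, so the step can be checked directly, and it fails. This is not detail left to an analysis plan; it is a stated result that disagrees with its stated inputs. The starting number is also larger than its own rates, power and significance level require.

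At stake is the traceability of the main planning number for patients. Someone who takes 350 as the requirement will misjudge the margin the trial has on its stated assumptions. That margin matters because the 25% control rate on which it depends sits awkwardly with the relapse expectation given elsewhere in the article.

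**Working it through.** **Inputs** (Sample size and power calculations, unless noted): p1 = 0.25, p2 = 0.10, two-sided 5%, power 80%, ρ = 0.05, m = 4, loss 10%. Allocation is 1:1 (Randomization procedure).

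**1. The plan's inflation step.**
Design effect = 1 + (4 − 1) × 0.05 = 1.15.
250 × 1.15 = 287.5, so 288. The article states 350, and 350/287.5 = 1.22, about 22% higher. The factor actually applied is 350/250 = 1.40.
After 10% loss: 288/0.9 = 320. The article's last step is consistent with its own 350, since 350/0.9 = 389, about 400. The break is therefore in the inflation step.

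**2. Cross-check on relatives.**
280 × 1.15 = 322, against a stated 320 (320/280 = 1.14). So about 1.15 is the article's own factor; it was not the one that produced 350.

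**3. The base of 250.**
n per arm = [1.96 × √(2p̄(1 − p̄)) + 0.8416 × √(p1(1 − p1) + p2(1 − p2))]² / (p1 − p2)², with p̄ = 0.175.
= (1.053 + 0.443)² / 0.0225 = 99.5, so 100 per arm and 200 in total.
With continuity correction: 112.5, so 113 per arm and 226 in total.
Other usual versions: 194 (unpooled or arcsine) and about 220 (Fisher's exact test, 110 per arm for 80.4%). None reaches 250.
Power of 250 individually randomised patients: 88% (84% with continuity correction).

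**4. Full chain on the stated inputs.**

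| Base N | × 1.15 | After 10% loss |
|---|---|---|
| 200 (no correction) | 230 | 256 |
| 226 (continuity correction) | 260 | 289 |
| 250 (as stated) | 288 | 320 |
| Article | 350 | about 400 |

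**5. Power at the planned size.**
400 enrolled less 10% = 360 followed; effective N = 360/1.15 = 313, about 156.5 per arm.
Power = Φ{[|p1 − p2| − 1.96 × √(2p̄(1 − p̄)/n)] / √[(p1(1 − p1) + p2(1 − p2))/n]}; for the continuity correction, subtract 1/n from the difference.

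| Rates | Uncorrected | Continuity-corrected |
|---|---|---|
| 25% v 10% (stated) | Φ(1.563) = 94% | Φ(1.411) = 92% |
| 40% v 25% (assumed) | Φ(0.885) = 81% | Φ(0.762) = 78% |

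The second row is a sensitivity check, not a scenario in the article. It takes nearly 60% not relapsing as 40% relapsing under TAU and keeps the same 15-point difference.

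**The case against.** **The 80% is not claimed for the final design.** The article attaches 80% only to the individually randomised 250, and calls 400 merely sufficient. This stands: on the stated inputs 400 is sufficient. A reader might infer that the trial is underpowered, or that a stated 80% for the clustered design is false. The text supports neither.

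**The base of 250 is only loose.** It is about 11% above the continuity-corrected 226, it errs on the safe side, and it came from an online calculator whose settings are not shown. This largely stands. The base is a lesser imprecision beside the inflation step.

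**An unstated allowance could explain 350.** The section excludes variation in cluster size. Even an assumed coefficient of variation of 1.0 gives only 250 × [1 + (2 × 4 − 1) × 0.05] = 338. Loss to follow-up is added after 350, so it is not already inside it. If some other allowance was made, it is not stated.

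**The two relapse rates may not be comparable.** The roughly 40% concerns relapse over the study period; the 25% concerns relapses and/or severe symptoms at 9 months, and different sources are cited. This stands to the extent that a contradiction is not proven. But if the and/or means a composite, over the same period it cannot be rarer than relapse alone, so the article should say how the two fit.

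**Tempting explanations.** A reader might infer that 350 came from a 40% v 25% scenario, because 304 × 1.15 is about 349. The article never mentions that scenario, it states a base of 250 rather than 304, and the match is lost with continuity correction (330 × 1.15 = 380). A reader might equally back-solve an ICC of 0.40/3 = 0.13; the article states 0.05, and its relatives' calculation agrees with 1.15. Nor is it true that the planned rate, ICC or effect is unknown: all three are stated, and only the resulting number fails to follow.

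**Conclusion.** The point holds as an arithmetic error in a stated planning figure. On the article's own formula and values, about 288 patients are required after clustering, not 350, and about 320 after loss, not 400. Starting from the base that the rates actually need, the requirement is 230–260, or 256–289 after loss.

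The direction is conservative. This rests on equal cluster sizes, ICC 0.05, four patients per cluster and 10% loss, all as stated. The comfortable margin also depends on the 25% TAU rate. If the control rate were 40% with the same absolute difference, power would be close to the conventional 80% rather than well above it. That is a reason to reconcile the two passages, not evidence that the trial is too small.

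**What to change.** Restate the patient paragraph as one chain: base N for 25% v 10% (200, or 226 with continuity correction, naming the method), design effect 1.15, N after 10% loss, and then the power that 400 enrolled patients give (about 92–94%). Alternatively, if something else lies behind 350, state that allowance.

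Add a sentence that reconciles the 25% TAU rate with the expectation in Primary outcomes that nearly 60% will not relapse, saying whether the outcome definition, time frame or source differs. If they do not differ, report the power at the higher control rate as well.

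The cost is the rewording of one paragraph. Enrolment, design and analysis are unaffected.
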